# Effectiveness and safety of mesenchymal stem/stromal cell for radiation-induced hyposalivation and xerostomia in previous head and neck cancer patients (MESRIX-III): a study protocol for a single-centre, double-blinded, randomised, placebo-controlled, phase II study

**DOI:** 10.1186/s13063-023-07594-5

**Published:** 2023-09-01

**Keywords:** Mesenchymal stem cells, Mesenchymal stromal cells, MSC, Xerostomia, Hyposalivation

## Abstract

**Background:**

A predominant side effect of radiotherapy for head and neck cancer is salivary gland hypofunction and xerostomia leading to debilitating oral disorders and impaired quality of life (QoL). Intraglandular mesenchymal stem cell therapy has shown promising results as a treatment for xerostomia.

**Methods:**

This is a randomised, double-blinded, placebo-controlled, parallel-group, prospective, single-centre trial investigating the safety, tolerability, and effectiveness of allogeneic stem cells as a treatment for radiation-induced hyposalivation and xerostomia for previous head and neck cancer patients.

We will include a total of 120 patients who previously have been treated with radiotherapy for a head and neck cancer in Denmark. Participants will be randomly assigned using block randomisation to one of two parallel groups in a 1:1 ratio to receive ultrasound-guided injection of allogeneic adipose-derived mesenchymal stem cell (ASC) (*n* = 60) or placebo (*n* = 60) into the submandibular glands. Placebo will consist of CryoStor10 (BiolifeSolutions), the freeze media for ASCs containing 10% dimethyl sulfoxide (DMSO). The primary endpoint is change in unstimulated whole saliva flow rate. The secondary endpoints are change in stimulated whole saliva flow rate, QoL, and composition of saliva. Further secondary endpoints are safety and immune response (human leukocyte antigen (HLA) response) to the stem cells will be assessed. Patients are evaluated at baseline (before treatment), after 4 months, and after 12 months. All study personnel, except study personnel thawing and preparing the treatment for injection, and participants will be blinded to group assignment. Unblinded study personnel will not participate in the outcome assessment.

**Discussion:**

The trials will investigate the efficacy and safety of ASC injection to the submandibular gland as a potential new treatment for post-radiation xerostomia. We hope the results will pave the way for a clinically relevant treatment to ameliorate patients with xerostomia, a severely hampering condition.

**Trial registration:**

The study is approved by the Danish Data Protection Agency (protocol number P-2020-1164), the National Ethics Committee protocol number: (Protocol number: 1802872), and the Danish Medical Agency (2018-000348-24). The protocol was registered at the ClinicalTrials.gov database (NCT04776538).

**Supplementary Information:**

The online version contains supplementary material available at 10.1186/s13063-023-07594-5.

## Introduction

### Background and rationale

The incidence of head and neck cancer is increasing in the Western World, including Denmark [1–3].

Approximately 80% of patients with head and neck cancer are treated with radiotherapy [4]. Despite the substantial improvement in ionising radiotherapy (IMRT, intensity-modulated radiation therapy), the radiation still leads to significant damage to healthy tissue, including the very radiation-sensitive salivary glands. Particularly, the acinar cells in the salivary glands suffer severe damage from radiation, and as these cells are the principal sites of fluid secretion, one of the most prevalent side effects of irradiation for head and neck cancer is hyposalivation and dry mouth syndrome, xerostomia [5, 6]. Xerostomia can lead to debilitating oral disorders and have a detrimental and lifelong impact on the quality of life (QoL) of the patients [7]. Xerostomia can cause impairment of normal oral functions including talking, chewing, and swallowing, can cause dental caries, and significantly decrease the quality of sleep [5, 8–10]. Currently, only symptomatic treatment is available to patients suffering from xerostomia, and therefore there is an immense, unmet need for new treatment strategies for hyposalivation and xerostomia [11, 12].

With the aim of restoring the salivary gland function in patients suffering from xerostomia due to radiotherapy, we have completed a randomised, placebo-controlled pilot study with 30 patients evaluating the safety and efficacy of ex vivo expanded autologous adipose-derived mesenchymal stem cells (ASCs) for radiation-induced xerostomia [13, 14]. This study showed that the treatment was safe without any serious adverse events. Also, patients treated with autologous ASCs had an increase in saliva production of 33–50%, and compared to the placebo group the patients treated with ASC experienced a significant improvement in their QoL as evidenced by reduced difficulties in eating [14]. However, we observed a substantial individual variation in ASC manufacturing in regard to cell yield, cell quality, and expansion time. We thus recently investigated the safety of allogeneic ASCs for the treatment of xerostomia in a clinical safety and feasible trial [15], including ten patients who received intraglandular injections of allogeneic ASCs. No serious adverse reaction occurred, and the efficacy data was similar to the results from our first trial with autologous ASCs with an increase in saliva production of 46% after 4 months. Patients also gained vital QoL measures regarding dry mouth, sticky saliva, and swallowing [15].

The purpose of this study is to assess the efficacy and safety of treatment with ASCs from healthy donors on radiation-induced salivary gland hypofunction and xerostomia in previous head and neck cancer patients in a randomised, double-blinded, placebo-controlled trial.

### Objectives

The trial aims to evaluate the effectiveness and safety of treatment with ASCs, as compared to a placebo in patients with radiation-induced salivary gland hypofunction.

The primary research hypothesis is as follows: Does treatment with ASCs, as compared to a placebo, lead to improvements in unstimulated whole salivary flow rate in patients with radiation-induced salivary gland hypofunction?

### Trial design

We will conduct a randomised, single-centre, double-blinded, placebo-controlled trial to compare the effectiveness, safety, and tolerability of allogeneic ASCs as a treatment for radiation-induced hyposalivation and xerostomia for previous head and neck cancer patients.

## Methods: participants, interventions, and outcomes

### Study setting

The study will take place at the Department of Otorhinolaryngology, Head and Neck Surgery & Audiology, Rigshospitalet, Denmark. All patients treated for a head and neck cancer in Denmark are eligible for inclusion if they fulfil the rest of the inclusion criteria.

The study protocol follows the SPIRIT guidelines (Standard Protocol Items: Recommendations for Interventional Trials) [16] (Supplementary 1).

### Eligibility criteria

The inclusion criteria are as follows:Are between 18 and 75 yearsPreviously have been treated with radiotherapy +/− chemotherapy for a head and neck cancerHave a 2 years follow-up without recurrenceHave a clinically reduced unstimulated whole saliva flow rate between 0.05 and 0.25 ml/min evaluated by sialometry

The exclusion criteria are as follows:Have had any cancer in the previous 4 years (not including the head and neck cancer and basocellular carcinomas)Receive xerogenic medicationsHave a penicillin or streptomycin allergyHave any other diseases of the salivary glands, e.g. Sjogren’s syndrome or sialolithiasisPreviously had submandibular gland surgeryPreviously had treatment with any type of stem cells in the saliva glandsAre pregnant or had a planned pregnancy within the 4 months study periodAre breastfeedingHave been smoking within the previous 6 monthsHave a current alcohol abuse (consumption must not exceed 7 units/week for women and 14 units/week for men (Danish National board health alcohol guidelines [17])Have any other disease/condition judged by the investigator to be grounds for exclusion

The criteria for withdrawal from the study are as follows:PregnancyInfection of the transplanted siteWithdrawal of consent from the participant^1^Cigarette smokingCancer (recurrence or new primary cancer, excluding basocellular carcinomas)

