### Interventions

Patients are randomised in a 1:1 ratio to receive one ultrasound-guided injection in each submandibular gland of ASCs or placebo. The injections are done without any anaesthesia or pain medications. ASCs are provided by the Cardiology Stem Cell Centre (CSCC) at Rigshospitalet. The donated adipose tissue will undergo a strict processing protocol for isolation of ASCs according to good manufacturing practice (GMP) in clean room facilities [18]. The cell products will come from a total of 4–5 healthy donors. Only one donor’s cells will be used in each cell vial. Placebo is consisting of CryoStor10 (BiolifeSolutions), the freeze media for ASCs containing 10% dimethyl sulfoxide (DMSO). The frozen suspension of ASCs or placebo will be thawed just before injection and 0.5 mL of ASC or placebo are injected into each submandibular gland. Patients receiving ASCs will receive a dose of 25 × 10^6^ cells per gland. Injections are carried out using a sterile 1 ml syringe and a sterile 23G (0.6 mm × 60 mm) needle on each side. A trained project nurse will thaw the frozen suspension of ASCs or placebo just before injection, and the syringes are covered in sterile green tape without information about the content of the syringes, to ensure that neither the patients nor the study staff can see the suspension injected. The injection of ASC or placebo is performed ultrasound-guided by free hand by a trained investigator (doctor) using a linear 9–18 MHz transducer. Patients are placed supine and the neck is slightly rotated and extended. The superficial part of the gland will be visualised, as being the part of the gland located between the digastric muscles and superficial to the mylohyoid muscle. The needle is placed in the gland from the anterior part towards the posterior, in a plane parallel to and superficially to the mylohyoid thus avoiding risk to the lingual artery. Injections are performed during a slow retraction of the needle placing the relevant volume in the gland.

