Patients are followed up after 4 month (+/− 14 days) and after 12 months (+/− 4 weeks). At the follow-up visits, patients will undergo saliva flow measurements, have analyses of saliva composition, have blood samples taken (for HLA antibodies), fill out QoL questionnaires, and have an ultrasound exam of the submandibular salivary glands. Lastly, all adverse events are monitored throughout the study period, from the time of treatment until the last day of follow-up (Fig. 1). When all study participants have completed the 4-month follow-up data will be unblinded. All data will be documented on-site in a secure web database, REDCap (Fig. 2).

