### Sample size

From our previous study MESRIX-I we assess to increase saliva production for whole unstimulated whole saliva flow rate (in ml/min) by about 33% or in absolute numbers from 0.125 to 0.155 after 4 months. The power calculation is based on a power of 0.8 and an alpha of 0.05. This means that the total number of patients included would have to be 100 (50 in each group). We expect a dropout rate of about 20% and therefore aim to include 120 participants in total.

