### Statistical methods

The analysis will be performed on the intention-to-treat population (ITT) and a statistical analysis plan will be completed before the end of the study. The primary endpoint is change in unstimulated whole saliva flow rate. The change in saliva flow rate from baseline to 4-month follow-up visit will be presented as change in mL/min and percentage change. The secondary endpoint of stimulated whole salivary flow rate will also be presented as change in mL/min and percentage change. Patient-reported outcome measurements will be evaluated as the changes from baseline to the 4-month follow-up visit and will be presented as a summary score ranging from 0 to 100. An ANCOVA model will be used to analyse continuous outcome measures (change from baseline). The baseline value will be included as a continuous covariate and the randomised treatment group will be included as a categorical variable. Data will be analysed after all patients have completed their 4-month follow-up time, and after the 12-month follow-up time.

Upon completion of the 4-month follow-up visit for all patients, the data will be unblinded, and an analysis of the 4-month follow-up data will be conducted. Subsequently, the long-term follow-up analysis will take place once all patients have completed their 12-month follow-up.

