### Harms

The included patients will be instructed to contact the principal investigator or a trained sub-investigator (doctor) in case they experience any events with possible relation to the trial treatment within the study period. Additionally, at the follow-up visits, all new medical events and any new medications that the patients have received throughout the trial will be thoroughly examined by the principal investigator or a trained sub-investigator. Any adverse events during or after the treatment in the trial will be noted and categorised into severity according to the Common Terminology Criteria for Adverse Events version 5.0 (CTCAE vs 5.0). The onset date, duration, and action taken for the adverse event will be documented.

Adverse events are defined as any untoward medical occurrence in the clinical trial period. All adverse events of CTCAE grade 3 and 4, and incidences considered related to this trial will be reported to the sponsor by the investigator immediately after they are discovered.

A serious adverse event is defined as a medical event that results in the following:DeathA serious deterioration in health including:Resulted in life-threatening illness or injuryRequired hospitalisation or prolongation of existing hospitalisationResulted in permanent impairment of body structure or body functionResulted in medical or surgical treatment to prevent the aboveAnything the principal investigator deems to be of clinically serious significance

Any serious adverse events will be reported to the Danish Medical Agency and the National Health Committee along with a report on the patients’ safety once a year. In case of a serious adverse event deemed related to the treatment, the Danish Medical Agency and the National Health Committee will be noted within 15 days or 7 days in case of death or life-threatening events.

Adverse events will be monitored for the first 4 months after the treatment. Serious adverse events will be monitored for the 12-month study period.

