### Ethical consideration and risk assessment

Participants will receive either ASCs or a placebo into the submandibular salivary glands by a needle, ultrasound-guided. The risk of infection and bleeding is estimated to be below 0.5%. In our previous studies, none of the 40 participants developed adverse reactions [14, 15]. During the injection of the transplant product (ASCs or placebo), the MESRIX-III participants may experience brief pain. There is a controversial debate regarding the effect of ASCs on cancer growth, as they have been shown to have both inhibitory and stimulatory effects [21–25]. However, multiple clinical trials have been conducted on different participant populations, including local injection of stem cells, involving more than 1000 participants, and no increase in the incidence of cancer has been detected. Extensive research has been carried out on the use of ex vivo expanded stem cells, and no data has been found indicating the malignant transformation of expanded human ASCs [26–28]. A study conducted by Katz et al. on a murine model showed that the injection of a high dose of MSC (240 × 106 MSC/kg) did not reveal any signs of cancer, organ toxicity, or change in body weight after 12 months [29].

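### Withdrawing patients from the study for pregnancy, infection, smoking or cancer after a one-off injection stops later data collection in consenting patients and weakens safety follow-up and analysis as randomised

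*Protocol article*

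**What the plan says.** The rule stands in the protocol article under Eligibility criteria, opened by the words "The criteria for withdrawal from the study are as follows". It lists five items: pregnancy, infection at the injected site, withdrawal of consent, cigarette smoking, and cancer (recurrence or a new primary, basocellular carcinoma excepted).

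Other sections bear on it:

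- **Interventions:** treatment is "one ultrasound-guided injection in each submandibular gland of ASCs or placebo", given on one occasion.
- **Statistical methods:** "The analysis will be performed on the intention-to-treat population (ITT"), with an ANCOVA on change from baseline for continuous outcomes.
- **Outcomes:** safety is a secondary endpoint at month 4 and is evaluated again at month 12, as are flow rate, questionnaires and immune response.
- **Participant timeline:** "all adverse events are monitored throughout the study period, from the time of treatment until the last day of follow-up".
- **Harms:** "Serious adverse events will be monitored for the 12-month study period"; other adverse events are followed for the first 4 months.
- **Ethical consideration and risk assessment:** "There is a controversial debate regarding the effect of ASCs on cancer growth", and, on the procedure, "The risk of infection and bleeding is estimated to be below 0.5" per cent.

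No section says whether a withdrawn patient still attends the 4- and 12-month visits.

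**The concern.** Study withdrawal and treatment discontinuation are different things. Where treatment is a single session, only the first has any meaning after the injection, and its effect is that later measurements are not taken.

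Four of the five triggers do not depend on the patient's wish to leave. They occur after randomisation. Two of them, infection at the injected site and cancer, could be consequences of the procedure or product. If such patients leave the study, their month-4 or month-12 flow rate, questionnaires and HLA antibodies are missing because of the rule and not by chance or choice. The course of the event and anything that follows it are no longer assured of observation.

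Two things are at stake. One is a safety comparison that may stop early in the patients who matter most to it. The other is a primary comparison that keeps all randomised patients in name but lacks outcomes for some of them by design.

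**Working it through.** **1. What the rule can mean.** Could it cover only the interval before injection, which may run to 90 days after the baseline visit (Participant timeline)? Infection at the injected site can arise only after injection, so the list must apply afterwards too. Could it mean stopping treatment? There is one session and no repeat dose. What remains is the end of study participation. Because withdrawal of consent is a separate item, the other four apply to patients who have not withdrawn consent.

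**2. The rule beside the analysis.** An ANCOVA on change from baseline to month 4 needs a month-4 value. A patient withdrawn before then has none. Such a patient can still belong to the intention-to-treat set, but only with a missing outcome.

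**3. The rule beside safety follow-up.** Harms and Outcomes run safety to 12 months and make no exception for withdrawn patients. Participant timeline ties adverse-event monitoring to the last day of follow-up, which for a withdrawn patient may be the day of withdrawal. The sections do not settle which reading governs.

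**4. The plan's own sample size.** The planned difference is 0.155 − 0.125 = 0.030 mL/min (Sample size: "in absolute numbers from 0.125 to 0.155 after 4 months"), with power 0.80, alpha 0.05 and 50 per arm. No SD is given, so 100 cannot be reproduced independently. Back-solving (two-sided alpha assumed): SD = 0.030 × √(50/2) / (1.960 + 0.842) = 0.150 / 2.802 = 0.0535 mL/min. The dropout step is 100 × 1.2 = 120; a 20% loss from 120 leaves 96, or 48 per arm.

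**5. What lost outcomes cost in power.** Power = Φ(0.030 / (SD × √(2/n)) − 1.960), with the back-solved SD:

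| Analysed per arm | Power |
|---|---|
| 60 | 86.6% |
| 54 | 82.9% |
| 50 | 80.0% |
| 48 | 78.4% |
| 45 | 75.7% |

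The expected 20% dropout already takes the trial just below 80%, so avoidable losses add to a thin margin.

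**6. What selection could do to the estimate.** The article gives no number of withdrawals under these criteria, so every input here is an assumption. Retained ASC patients are given +0.030 mL/min and retained placebo patients 0, with 60 per arm.

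- *ASC withdrawals only, with change 0:* overstatement = w × 0.030 / 60. This is 0.0005 for w = 1, 0.0015 for w = 3 and 0.003 for w = 6 (10% of 0.030).
- *Five ASC withdrawals with change −0.030, none on placebo:* full ASC mean (55 × 0.030 − 5 × 0.030)/60 = 0.025, against 0.030 analysed.
- *Five such withdrawals in each arm:* placebo mean −5 × 0.030/60 = −0.0025, so the full difference is 0.025 + 0.0025 = 0.0275, against 0.030 analysed. The overstatement is 0.0025/0.0275, about 9%.
- *Five on placebo only:* full difference 0.030 + 0.0025 = 0.0325, against 0.030 analysed. The effect is now understated.

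The size, and even the sign, depends on inputs that the document does not supply.

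**7. How often infection would trigger the rule.** Taking the stated bound as per patient, 0.005 × 120 = 0.6 infections at most; taking it per gland, 0.005 × 240 = 1.2. Infection alone would move the primary estimate little. No corresponding figure is given for cancer, smoking or pregnancy.

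**8. Timing.** The article appeared on 1 September 2023, and Trial status expects the last visit in February 2024. With the 12-month window of ±4 weeks, the last injection falls no later than about the end of March 2023. The last month-4 visit (±14 days) then falls no later than about mid-August 2023, before publication.

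**The case against.** Several stronger readings are tempting, and the document does not support them.

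- **That collected data are discarded.** Nothing says so. The only data not saved are those of patients who fail screening (Participant timeline). Harms requires adverse events to be noted with onset, duration and action taken, so the triggering infection or cancer would itself be recorded. The loss concerns what comes later.
- **That the rule flatly contradicts intention to treat, or turns the ANCOVA into a completers analysis.** Withdrawn patients can stay in the analysis set with missing outcomes, and handling those is ordinary content of an analysis plan that is not shown.
- **That the effect would be overstated by 20%, or that the expected dropout of about 24 of 120 patients reflects these triggers.** The 20% needs five ASC withdrawals, none on placebo, and an invented change. The dropout figure is overall and is not linked to these criteria.
- **That the article ignores the cancer question.** It also reports that trials in more than 1000 participants detected no increase in cancer incidence, and that none of its own 40 earlier participants had an adverse reaction. Entry requires two years without recurrence and no smoking in the previous six months, so triggers may be few.

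It can also be said that an article condenses the full protocol, which may describe follow-up after withdrawal, and that the note attached to withdrawal of consent is not shown. Both are fair cautions. But the rule is stated here, not left out, the note is attached only to the consent item, and an analysis plan cannot recover visits that were never made. The timing objection also stands in part: an amendment at publication could no longer rescue a missed month-4 visit.

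**Conclusion.** The point holds as a weakness in a stated rule. On its plain reading, the rule ends outcome and safety data collection in consenting randomised patients after pregnancy, infection at the injected site, smoking or cancer, although no treatment remains to be stopped. It undermines the intention-to-treat analysis in principle and the 12-month safety evaluation in practice, most of all for infection and cancer.

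Bias in the primary estimate is probably small and cannot be quantified from the document. The main harm is to safety follow-up and to analysis as randomised. The conclusion rests on reading withdrawal from the study in its ordinary sense. If the full protocol keeps these patients under observation, the remedy is only to say so.

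**What to change.** Reconcile Eligibility criteria with Outcomes, Participant timeline, Harms and Statistical methods:

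1. State that only withdrawal of consent ends data collection. Record pregnancy, infection, smoking and cancer as intercurrent or safety events.
2. Keep willing and able patients in the 4- and 12-month assessments already scheduled. For this trial, that now means the remaining 12-month visits.
3. Include all available data, as randomised, in the intention-to-treat ANCOVA.
4. Tabulate infection and cancer (recurrence or new primary) by arm through 12 months.
5. Report how many patients were withdrawn under each criterion, by arm, with a sensitivity analysis for their missing month-4 values, such as a tipping-point analysis. Specify it before the month-4 data are unblinded if that is still possible; otherwise label it as added later.

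This concerns data collection and analysis only; clinical care of these events is unchanged, and so is the planned sample size. The cost is amended wording, a few more visits and some added noise from values measured after these events. A supportive analysis without those values can show how much they matter.
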